#### **Primary outcome:**

Statistically significant difference in QuickDASH score is 6.8 (18) at 12 months FU.

#### **Secondary outcome:**

Difference in active ROM in comparison to uninjured arm, PedsQL, PEDS QL Pain module, Cosmetic VAS, MEPS, need for additional procedures.

#### **Sample size**

Based on the results of Nikolas et al (2020) and Aasheim et al (2014) we assume clinically significant difference between the groups to be 6,8 and the standard deviation of the QuickDASH score to be 10

points. With 0,05 significance level and 80% power a non-inferiority comparison would require 27 patients per group. Allowing a 20% dropout rate the required sample would be 30 patients per group.

For subgroup analysis (less than 12 years vs. 12 years and over) 30 patients per age group needs to be collected. Assuming 50-50 split in the patients between the age groups the sample size would be 60 per ORIF and non-operated equaling a total of 120 patients.

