## **METHODS AND ANALYSIS**

### **Study design:**

The study is designed as a multicenter parallel-group non-inferiority randomized controlled trial (RCT) that complies with the CONSORT guidelines (Figure 1). A patient preference arm will be available. Patient recruitment will be done at all university hospital areas of Finland (Helsinki, Kuopio, Oulu, Tampere, Turku). The study is coordinated by Helsinki University Central Hospital, Children's Hospital pediatric orthopedic unit. Trial data analysts and person performing the recruitment will be unaware of the assigned treatment.

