### **Statistical analysis:**

Data will be analyzed by using the Wilcoxon rank-sum test in Python 3.8. (Python Software Foundation, Wilmington, Delaware, U.S.A). Our hypothesis is that there is no difference in outcome between non-operative versus ORIF. Level of significance is set at  $p < 0.05$ .

Both treatment groups will be internally analyzed for differences in primary outcome regarding age (less than 12 years vs. 12 years and over) at time of injury and amount of initial fracture displacement (mm). Depending on group size, patient choice arm can be merged for analysis to same RCT group.

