## **CONCLUSION**

The goal of this study is to compare two well-established treatment methods of dislocated non-incarcerated humeral medial epicondyle fractures in 7-16 year old patients.

**Figure 1** Flow chart of the study

[figure not shown]

| Table 1                            | Data collection time points |                 |                 |                 |                 |                     |                     |
|------------------------------------|-----------------------------|-----------------|-----------------|-----------------|-----------------|---------------------|---------------------|
|                                    | Baseline                    | Treatment day 0 | 1. Checkup 1 mo | 2. Checkup 3 mo | 3. Checkup 6 mo | 4. Checkup 12months | 5. Checkup 24months |
| Diagnosis, eliqibility             | x                           |                 |                 |                 |                 |                     |                     |
| Randomisation                      | x                           |                 |                 |                 |                 |                     |                     |
| Surgery or non-operative treatment |                             | x               |                 |                 |                 |                     |                     |
| Physical examination               | x                           |                 | x               | x               | x               | x                   | x                   |
| Questionnaires                     |                             |                 | x               | x               | x               | x                   | x                   |
| Computer tomography                | x                           |                 |                 |                 |                 |                     |                     |
| Standard radiograph                | x                           |                 | x               | x               | x               | x                   | x                   |

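### The trial is declared and sized as a one-direction non-inferiority comparison, but no reference arm is named, 6.8 has no sign, and the stated hypothesis and test are symmetric

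*Protocol*

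**What the plan says.** The Study design section of the protocol declares a parallel-group non-inferiority RCT. The Sample size section builds on this: "we assume clinically significant difference between the groups to be 6,8", with an SD of 10, and then "With 0,05 significance level and 80% power a non-inferiority comparison would require 27 patients per group". It goes on to 30 per group for dropout, and to 60 per arm (120 in all) so that each age group has 30 per arm.

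No section at hand names a test arm and a reference arm. Randomization assigns 1:1 to surgery or casting without calling either one the control. The Ethics and dissemination section says there is no consensus and that both treatments are established. The Conclusion puts the aim evenly: "The goal of this study is to compare two well-established treatment methods".

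The 6.8 has no sign in the Sample size section, and none in the Primary outcome section either: "Statistically significant difference in QuickDASH score is 6.8 (18) at 12 months FU".

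The Statistical analysis section names the Wilcoxon rank-sum test with significance at p<0.05 and states: "Our hypothesis is that there is no difference in outcome between non-operative versus ORIF". It mentions neither a margin nor a direction.

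**The concern.** A non-inferiority claim has three parts: the arm being tested, the arm it is tested against, and the amount by which it may be worse. The protocol gives only the size of the third. The reference cannot be filled in from usual practice, because the protocol itself says that practice varies and that both treatments are established.

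The hypothesis of no difference is symmetric. The Wilcoxon test looks for departure from no difference and makes no use of 6.8. A non-significant result would not show that either arm is within 6.8 of the other, and a significant one would not show that the margin had been exceeded. The analysis as written therefore does not test the claim for which the trial is declared and sized.

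Replacing the test with a confidence interval would not settle this by itself, since the protocol would still not say which limit decides. At stake is what the trial may conclude. That casting is not inferior to surgery and that surgery is not inferior to casting are different messages, and the choice between them would remain open after the data are known.

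**Working it through.** **Inputs.** From Sample size: difference 6.8, SD 10, significance level 0.05, power 80%, dropout 20%, 60 per arm and 30 per arm in each age group. From Randomization: ratio 1:1. Not stated: the sidedness of 0.05 and the assumed true difference. A true difference of 0 is assumed here because it reproduces the protocol's figure.

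**1. The protocol's own figure.** For one direction, n per group = 2 × [SD × (z for alpha + z for power) / margin]².
- One-sided 0.05: 2 × [10 × (1.645 + 0.842) / 6.8]² = 26.7, so 27. This matches.
- One-sided 0.025: 2 × [10 × (1.960 + 0.842) / 6.8]² = 34.0, so 34. A two-sided 0.05 test for a difference of 6.8 also needs 34.

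The 27 is therefore a single one-sided 5% test. (A one-sided 5% test to detect a difference of 6.8 has the same arithmetic; it too has one direction.)

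**2. Power for one direction and for both.** SE = 10 × √(2/n). One direction: Φ(6.8/SE − 1.645). Both directions (equivalence within ±6.8, two one-sided 5% tests): 2 × Φ(6.8/SE − 1.645) − 1. The numbers after loss are 60 × 0.8 = 48 and 30 × 0.8 = 24.

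| Per group | What it is | SE | One direction | Both directions |
|---|---|---|---|---|
| 27 | quoted requirement | 2.72 | 80.3% | 60.7% |
| 60 | planned per arm | 1.83 | 98.1% | 96.2% |
| 48 | planned, after 20% loss | 2.04 | 95.4% | 90.8% |
| 30 | per arm in one age group | 2.58 | 83.9% | 67.7% |
| 24 | age group, after 20% loss | 2.89 | 76.1% | 52.3% |

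At 27 per group, t-based simulation gives 59% for both directions, close to the 61% above. Both directions at 80% would need 2 × [10 × (1.645 + 1.282) / 6.8]² = 37.04, so 38 per group.

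**3. Sensitivity of the overall figure.** If the true difference were 2 points (an assumed value), two-direction power would be about 84% at 60 per arm and 76% at 48. With each test at one-sided 0.025 and true difference 0, it would be 92% and 83%.

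**4. What an unnamed direction allows.** Both directional claims fail together only if the 90% interval reaches past −6.8 and +6.8 at once, so that its half-width is at least 6.8. The half-width is 1.645 × SE: 4.48 at 27 per group, 3.36 at 48 and 3.00 at 60. In simulation at the planning SD, at least one direction passed in at least 99.99% of trials at true differences of 0, 3.4, 6.8 and 10. This stops holding only if the observed SD exceeds about 15 at 27 per group, or about 20 at 48.

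**5. Error of a single claim.** At a true difference of 6.8, the worse arm was wrongly declared non-inferior in about 5% of simulated trials, and at 10 in 0.3% or fewer. The two directional null hypotheses cannot both be true, so testing both does not add their errors.

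**The case against.** The strongest reply is that this is a matter of wording. The text at hand begins at the methods, Figure 1 is not shown, and the SAP is not at hand, so the direction may be stated elsewhere. The order of the arms in the hypothesis may also hint that casting is the test treatment. It is true that a direction could be stated elsewhere, and that the exact decision rule is often left to an SAP. But which arm is tested against which is the trial's hypothesis. The protocol does not merely leave it open: it sizes a directional question and then states a symmetric one. Word order designates nothing.

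It can also be said that two established treatments do not rule out non-inferiority, since either could serve as the reference. That is correct. The fault is that neither is chosen.

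Two stronger readings are tempting, and the protocol supports neither:
- **That the trial is under-powered.** A reader might infer from 61% at 27 per group that the stated 80% is lost. But the protocol goes on to plan 60 per arm, and the overall two-direction power at true difference 0 is then above 80% even after dropout. The shortfall within an age group matters only if a treatment comparison is made there. The Statistical analysis section describes age comparisons inside each treatment arm.
- **That the trial cannot fail.** A reader might infer from step 4 that success is guaranteed. But no section declares that either direction passing counts as success. When one arm really is worse by the margin or more, the claim that passes is nearly always the true one, namely that the better arm is not inferior. This is no false-positive problem.

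**Conclusion.** The point holds as an inconsistency between declared design, sample size and analysis. The 27 per group is a one-direction calculation; no arm is named as the reference in the text at hand; 6.8 is unsigned; and the stated hypothesis and test are symmetric and make no use of the margin. The practical consequence is that the direction of any non-inferiority claim is open to choice after the data are seen.

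Its size is limited. A single directional claim keeps an error of 5% or below. If the symmetric question is meant, the planned 120 patients give about 96% power, or 91% after 20% loss. The stated 80% does not apply to that question at 27 per group (61%) or within one age group (68%, or 52% after loss). The power figures assume SD 10, true difference 0, one-sided 0.05 and a normal approximation. The missing direction depends on none of these. The matter should be settled before unblinding.

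**What to change.** Amend the Study design, Sample size and Statistical analysis sections in one of two ways. The choice is the sponsor's.

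- **Non-inferiority.** Name the test arm and the reference arm. Define the 12-month QuickDASH difference as test minus reference, and say which sign counts against the test arm. State that non-inferiority is shown if the relevant limit of the confidence interval, at the one-sided 0.05 used for sizing (a 90% two-sided interval), is within 6.8. Make that direction the only primary claim. The 27 per group then stands as calculated.
- **Equivalence.** Declare it as such and require both limits to lie within −6.8 to +6.8. State power for the planned size after dropout: about 91% overall at 48 per arm, and about 52% at 24 per arm for any treatment comparison within an age group.

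In either case, reword the hypothesis in the Statistical analysis section to match, and describe 6.8 as the margin in the Primary outcome section.

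The cost is a few sentences before unblinding and no extra patients. The small downside is giving up the other directional claim or, under equivalence, stating a lower power within age groups.

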## **Randomization**

After agreeing to participation in the trial patients are randomized according to a computer-generated randomization list to either operative or non-operative treatment. Randomization ratio is 1:1.

Randomization is performed by the recruiting physician who is blinded to the intervention.

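### The sample-size section inflates 27 to 30 per group for 20% dropout; the correct figure is 34, so each age-by-treatment cell ends with 24 evaluable patients, below the 27 required

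*Protocol*

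**What the plan says.** The Sample size section of the protocol takes a QuickDASH difference of 6.8 points and a standard deviation of 10, and concludes: "With 0,05 significance level and 80% power a non-inferiority comparison would require 27 patients per group". The next sentence adds the allowance for losses: "Allowing a 20% dropout rate the required sample would be 30 patients per group".

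The section then turns to the age subgroups (under 12 years, and 12 years and over). It asks for 30 patients in each age group, assumes an even split by age, and arrives at "60 per ORIF and non-operated equaling a total of 120 patients". The total is therefore the inflated figure of 30 multiplied by four age-by-treatment cells.

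No other section gives a different dropout rate or corrects the 30. The Statistical analysis section names the Wilcoxon rank-sum test and a 0.05 significance level. It describes the age analysis as one carried out inside each treatment group.

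**The concern.** Thirty patients less 20% is 24, not 27, so the dropout rate and the sample size stated in the same sentence cannot both be right. The slip carries forward, because 30 is the building block of the 120 total.

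What is at stake is the age-subgroup analysis, which is the stated reason for going from 30 to 60 per arm. If losses reach the rate the protocol itself assumes, every cell falls below the number the protocol says a comparison needs. A reader would nevertheless take from the text that each age group is sized to the same standard as the two-group calculation.

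**Working it through.** **Inputs (protocol)**
- Margin 6.8 points: "we assume clinically significant difference between the groups to be 6,8" (Sample size). The true difference is taken as 0.
- Standard deviation 10: "the standard deviation of the QuickDASH score to be 10" (Sample size).
- Alpha and power: "With 0,05 significance level and 80% power" (Sample size). Sidedness is not given.
- Allocation: "Randomization ratio is 1:1" (Randomization).
- Dropout 20% (Sample size).

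**Step 1: reproduce the 27.** n per group = 2 × SD² × (z_alpha + z_power)² / margin².
- One-sided 0.05: 2 × 100 × (1.645 + 0.842)² / 6.8² ≈ 26.7, so **27**. This agrees with the protocol.
- One-sided 0.025 or two-sided 0.05: 2 × 100 × (1.960 + 0.842)² / 6.8² ≈ 33.9, so 34 before any dropout. This does not agree.

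The 27 therefore rests on one-sided 0.05, and the fault lies in the dropout step alone.

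**Step 2: the dropout step.**
- Correct inflation: 27 / (1 − 0.20) = 33.75, so **34**.
- Common shortcut: 27 × 1.20 = 32.4, so 33.
- Stated: 30. This equals 27 / 0.90, a 10% allowance.
- Check in reverse: 30 × 0.80 = **24** evaluable.

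**Step 3: carry it through.** Four cells of 30 give 120. Four cells of 34 give 136, which is 68 per arm. With 120 enrolled and 20% lost, 24 remain per cell and 48 per arm.

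**Step 4: power for a difference or margin of 6.8.** By the normal approximation, power = Φ(6.8 / (10 × √(2/n)) − z_alpha). For n = 24 the first term is 6.8 / 2.887 = 2.356, so at one-sided 0.05 power = Φ(2.356 − 1.645) = Φ(0.711) = 0.761. The t-test column uses the noncentral t distribution. The Wilcoxon column multiplies n by 3/π, the test's efficiency under normal data.

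| Evaluable per group | Alpha | Normal | t-test | Wilcoxon |
|---|---|---|---|---|
| 27 (cell, as required) | one-sided 0.05 | 80.3% | 79.4% | 78.7% |
| 24 (cell, after 20% loss) | one-sided 0.05 | 76.1% | 75.0% | 74.4% |
| 24 (cell, after 20% loss) | two-sided 0.05 | 65.4% | 63.5% | 63.4% |
| 48 (whole arm, after 20% loss) | one-sided 0.05 | 95.4% | 95.2% | 94.6% |
| 48 (whole arm, after 20% loss) | two-sided 0.05 | 91.5% | 90.9% | 90.2% |

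**The case against.** The strongest reply is that nothing primary is harmed. The main comparison plans 60 per arm against a stated need of 27, and it still has 48 per arm after a 20% loss. That is correct, and it settles the severity: the error costs about 4 points of power, method for method, in a subgroup analysis. A reader who sees a wrong sample-size figure might infer that the trial is underpowered for its primary outcome; the figures show the opposite.

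A second reply is that the protocol never states 80% power for the age subgroups. It attaches 80% to a two-group comparison and then reuses the resulting 30 per cell. This also stands: the 80% is implied by the sizing, not promised. For the same reason, a reader might combine the two age groups and calculate the chance that both show non-inferiority. The protocol sets no such requirement, so a joint probability would answer a claim that it does not make.

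A third reply is that 76% is not the power of the analysis described. Sidedness is not stated. The Statistical analysis section compares younger with older patients inside each arm, which is a test of difference and not treatment non-inferiority within an age group. It also names the Wilcoxon test. This is fair, and it is why the power must be quoted with its assumptions. It does not rescue the 30: under either reading the comparison is 24 against 24, and a two-sided test has less power, not more.

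No part of the reply makes 30 consistent with 27 and a 20% loss.

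**Conclusion.** The figure of 30 per group is wrong as written. At 20% dropout, 27 evaluable patients require 34 enrolled; 30 is right only for 10%. Through the four cells the error sets the total at 120, where the protocol's own logic gives 136.

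At the stated dropout each cell keeps 24 evaluable patients. Cell-level power is then about 74–76%, on three assumptions: one-sided alpha 0.05 (inferred because it reproduces 27), a treatment comparison within each age group with no true difference, and an even age split. For a two-sided 0.05 test of a 6.8-point difference, such as younger against older within an arm, it is about 63–65%; most of that further drop comes from the sidedness and not from the dropout slip. The Wilcoxon figures also assume roughly normal scores.

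The primary comparison is unaffected, at about 95% one-sided or 90–91% two-sided. The point should be fixed because the sample-size justification contradicts itself, but it does not put the trial's main conclusion at risk.

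**What to change.** Correct the Sample size section in one of two ways, neither of which enrols more patients.

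1. State that 30 per group, 120 in total, allows for 10% dropout. This is acceptable only if the sponsor can support that rate; the protocol gives no basis for it, and choosing it merely because it fits the number would not be a justification.
2. Keep 20% dropout and 120 patients, and restate what they deliver: 24 evaluable per age-by-treatment cell with power of about 75%, and 48 per arm with overall power of about 95%, both at one-sided 0.05.

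Either way, name the sidedness of alpha and say which comparison each power figure refers to, treatments within an age group or age groups within an arm. If the second is meant and tested two-sided, the subgroup figure to report under option 2 is about 63–65%.

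The cost is a few restated numbers and a slightly less favourable subgroup claim. For reference, the enrolment consistent with 27 evaluable per cell at 20% dropout is 34 per cell and 136 in total, which is 16 more patients; the primary comparison does not need them.

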### **Statistical analysis:**

Data will be analyzed by using the Wilcoxon rank-sum test in Python 3.8. (Python Software Foundation, Wilmington, Delaware, U.S.A). Our hypothesis is that there is no difference in outcome between non-operative versus ORIF. Level of significance is set at  $p < 0.05$ .

Both treatment groups will be internally analyzed for differences in primary outcome regarding age (less than 12 years vs. 12 years and over) at time of injury and amount of initial fracture displacement (mm). Depending on group size, patient choice arm can be merged for analysis to same RCT group.

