## **Baseline**

Standard anterior-posterior and lateral radiographs of the elbow will be obtained after closed reduction of the possible elbow dislocation. All participants in either the RCT or patient's choice arm undergo cone-beam or normal computer tomography (CT) before treatment initiation. Initial fracture dislocation will be calculated from the CT scans in three planes (anterior-posterior, cranial-caudal and medial-lateral) and both radiographs (anterior-posterior and lateral) using the method described by Edmonds et al (2010). Date of injury, method of injury, patient's age at time of injury, sex, injured side, dominant hand and main sport or musical instrument as well as level will be documented. Motor and sensory function as well as range of motion of both upper limbs will be assessed. Carrying angle (degrees) and valgus stress test will be assessed if possible for both limbs.

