### **Outcome measure**

Follow-up is set at 1, 3, 6, 12 and 24 months from initiation of treatment with the option of ending the FU at 12 months if patients is pain free with full ROM in relation to uninjured side. Elbow standard radiograph (anterior-posterior and lateral) are taken at each appointment from 3 months on until bone union is achieved or trial ends (Table 1).

Patients will be examined at the pediatric orthopedic outpatient clinic. Upon each appointment active and passive ROM of both upper limbs (elbow extension-flexion, pro-supination, wrist extension-flexion) as well as carrying angle are measured using a goniometer. Stability of both elbows are assessed using the moving valgus test and the valgus stress test. Distal sensation is examined by Semmes-Weinstein monofilaments. Signs of cold intolerance will be assessed. Grip strength is measured with a dynamometer.

Patients and guardians are requested to answer the following patient reported outcome measures at each appointment; QuickDASH, Pediatric Quality of Life InventoryTM (PedsQL), PedsQL Pediatric Pain Questionnaire, cosmetic visual analogue scale (VAS 0-100) and Mayo elbow performance score (MEPS).

Time of returning to main sport or music and its level will be documented (weeks). Any adverse effects (wound infection, nerve damage) are documented as well as hardware problems and possible hardware removal as well as conversion of treatment during FU (cast to ORIF or ligament reconstruction).

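### The named analysis is an unadjusted Wilcoxon test of no difference: it gives no interval to set against the 6.8-point margin and leaves age, displacement and earlier QuickDASH scores out of the treatment comparison

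*Protocol*

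**What the plan says.** Protocol, Study design, calls the trial a parallel-group non-inferiority RCT. Sample size sizes it that way: "we assume clinically significant difference between the groups to be 6,8", with "the standard deviation of the QuickDASH score to be 10" points, and "With 0,05 significance level and 80% power a non-inferiority comparison would require 27 patients per group". The sidedness of the 0.05 is not given.

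Statistical analysis then names one method: "Data will be analyzed by using the Wilcoxon rank-sum test in Python 3.8". The stated hypothesis is that outcome does not differ between the treatments, judged at p < 0.05. No estimate, interval or covariate is attached to that comparison. Age group and displacement do appear in this section, but in analyses inside each treatment group.

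The data for a fuller comparison are already planned:
- Baseline: age at injury is recorded, and "Initial fracture dislocation will be calculated from the CT scans in three planes".
- Outcome measure: "Patients and guardians are requested to answer the following patient reported outcome measures at each appointment", and QuickDASH is one of them. Visits are at 1, 3, 6, 12 and 24 months, and the 24-month visit can be waived.
- Table 1 schedules no questionnaire at baseline, so there is no baseline QuickDASH to adjust for.

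The primary outcome is QuickDASH at 12 months.

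**The concern.** There are two consequences, of unequal weight.

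First, a non-inferiority claim needs an estimate of the difference and a confidence limit on the favourable side of the margin. A p-value for a null of no difference supplies neither. A non-significant result could be read as success when the data are merely imprecise, and the 6.8 points that drove the sample size would play no part in the conclusion.

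Second, a two-sample rank-sum test has no term for covariates or repeated visits. The protocol treats age and displacement as relevant enough to examine the primary outcome by both, but the comparison of treatments does not use them. Nor does it use the earlier QuickDASH scores, which carry information about children who lack a 12-month score. What may be lost is precision, chiefly in the age subgroups for which the trial was enlarged to 120.

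**Working it through.** **Inputs.** From Sample size: margin 6.8, SD 10, 80% power, 20% dropout, 30 per arm in each age group, 60 per arm overall. From Randomization: "Randomization ratio is 1:1". The documents give no correlations, so these are assumed: R² is the share of 12-month variance explained by age and displacement, and ρ is the remaining correlation of earlier scores with the 12-month score. True difference is taken as 0.

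**1. The plan's own figure.** n per group = 2[SD(z₁₋α + z₀.₈)/6.8]². One-sided α = 0.05: 2[10(1.645 + 0.842)/6.8]² = 26.7, so 27, which agrees. One-sided 0.025 gives 33.9, so 34. The plan therefore appears to work at one-sided 5%, and power below is at that level.

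**2. Completers.** With 20% lost, 60 × 0.8 = 48 per arm overall and 30 × 0.8 = 24 per arm in an age group.

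**3. What a test of no difference can miss.** The normal-theory interval for a difference in means is used as a stand-in, since the rank test yields no such interval as planned.
- 48 per arm: SE = 10√(2/48) = 2.04. A two-sided 5% test is non-significant below 1.986 × 2.04 = 4.05. The one-sided 95% limit clears 6.8 only if the observed unfavourable difference is below 6.8 − 1.661 × 2.04 = 3.41.
- 24 per arm: SE = 10√(2/24) = 2.89. The two thresholds are 2.013 × 2.89 = 5.81 and 6.8 − 1.679 × 2.89 = 1.95.

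So unfavourable differences of 3.41 to 4.05 overall, and 1.95 to 5.81 in an age group, are non-significant without showing non-inferiority.

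**4. Possible precision gain.** Let m = 0.2 be the share missing only the 12-month score, missing at random and seen earlier. The variance relative to an unadjusted comparison of completers is

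(1 − R²)[1 + (m/(1 − m))(1 − ρ²)] / [1/(1 − m)] = (1 − R²)[1 + 0.25(1 − ρ²)]/1.25.

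Power uses the noncentral t distribution, with SD² multiplied by this ratio.

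| R² | ρ | Variance ratio | Power, 48 per arm | Power, 24 per arm |
|---|---|---|---|---|
| none | none | 1 | 95.2% | 75.0% |
| 0 | 0.3 | 1.2275/1.25 = 0.982 | 95.5% | 75.7% |
| 0 | 0.5 | 1.1875/1.25 = 0.950 | 96.0% | 76.9% |
| 0.10 | 0.5 | 0.9 × 1.1875/1.25 = 0.855 | 97.3% | 80.6% |
| 0.20 | 0.6 | 0.8 × 1.16/1.25 = 0.742 | 98.6% | 85.3% |

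The last column is somewhat optimistic: age group is constant within a subgroup and explains nothing there. No degrees of freedom are charged for the model terms.

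**5. The baseline row is a t-test, not the Wilcoxon test.** Simulation with a shift of 6.8, SD 10, 24 per arm and one-sided 5%, for assumed distributions and across separate runs, gives for Wilcoxon against t:
- normal: 72–73% against 74–75%
- gamma, shape 2: 84–85% against 74–75%
- exponential: 92% against 75–78%

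Under skew of this kind the rank test's advantage can exceed the gain in step 4.

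**The case against.** An unadjusted rank test of randomised arms is valid, so adjustment is a matter of efficiency, and covariates and missing-data methods are commonly left to a statistical analysis plan that is not shown here. That stands as far as omissions go. But the protocol fixes a method and a hypothesis, and these do not match its declared design; a later plan that reported an adjusted difference would depart from the named test.

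A Wilcoxon test can be inverted to give a Hodges–Lehmann shift with an interval. True, but the protocol plans only a test at p < 0.05 and does not refer the result to 6.8 points.

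The gain is small where power is already high, and the 75% in the subgroup is not the Wilcoxon test's doing. This stands. It arises because 30 per group does not cover 20% dropout: 27/0.8 = 33.75, so 34.

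Four stronger readings are tempting and not supported:
- That dropouts are discarded. "Allowing a 20% dropout rate" appears only in the sample size, and the protocol states no rule for missing scores. A child without a 12-month score adds nothing to this test unless a value is imputed; more cannot be said.
- That randomisation is simple, so imbalance is likely. The protocol describes a computer-generated 1:1 list and does not say whether it is blocked or stratified.
- That age and displacement are ignored altogether. They are used within each arm.
- That the Wilcoxon test is less precise than a model. Step 5 shows that this depends on the shape of the scores.

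**Conclusion.** The point holds in two parts. The firmer part rests on the protocol's text alone: the only named analysis tests for no difference and, as written, gives nothing to compare with the 6.8-point margin. The second part is a worthwhile efficiency gain of uncertain size. At one-sided 5%, SD 10 and 20% dropout, with R² from 0 to 0.20 and ρ from 0.5 to 0.6, whole-trial power moves from about 95% to 96–99%. In an age subgroup of 24 completers per arm it moves from 75% to about 76–85%, less an allowance for age being constant there; the low end is about the same if ρ is only 0.3. These figures assume every dropout was seen before 12 months and is missing at random. The validity of the randomised comparison is not in question, and the documents do not establish that the rank test loses power.

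**What to change.** In Statistical analysis, define the primary analysis as the difference between arms in 12-month QuickDASH, from a repeated-measures model of the 1, 3, 6 and 12 month scores with treatment, visit, treatment-by-visit, age and initial displacement. The earlier scores enter as repeated outcomes, not as adjustment covariates, because they are measured after randomisation. Use bootstrap or robust standard errors. Report the confidence interval against 6.8 points and state the one-sided level. For the planned age subgroups add a treatment-by-age-group term, allowed to vary by visit so that it can be read at 12 months; without it the model gives no subgroup effect. Keep the Wilcoxon test as a sensitivity analysis.

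The cost is revised wording and modest programming, with no new data or visits. The downside is reliance on a model for scores that may be skewed. Robust or bootstrap errors protect the interval but do not recover the power a rank test can have in that case, which is a reason to retain the Wilcoxon result alongside.
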